# Deep brain stimulation of the posterior subthalamic area and the thalamus in patients with essential tremor: study protocol for a randomized controlled pilot trial

**DOI:** 10.1186/s13063-016-1599-3

**Published:** 2016-09-29

**Keywords:** Deep brain stimulation (DBS), Ventral intermediate nucleus of the thalamus (VIM), Posterior subthalamic nucleus (PSA), Essential tremor (ET), Zona incerta (Zi), Stimulation-induced side effects, Constant current stimulation, Crossover study

## Abstract

**Background:**

Deep brain stimulation (DBS) of the ventral intermediate nucleus (VIM) of the thalamus is effective in medication refractory essential tremor (ET). In recent years, evidence has accumulated that the region ventral to the VIM, the posterior subthalamic area (PSA), might be an equally or even more effective target for electrode implantation. However, this evidence is primarily based on case series, cross-sectional observations, and retrospective data.

**Methods/design:**

A prospective crossover pilot study investigating the effects of PSA stimulation in medication refractory ET patients was designed. In this study, bilateral electrodes are implanted such that at least one of the electrode contacts is located in the PSA and VIM, respectively. This implantation approach allows (1) a prospective double-blind investigation of the effects of PSA stimulation compared to baseline, as well as (2) a crossover comparison between VIM and PSA stimulation with respect to tremor suppression and side effect profiles.

**Discussion:**

The results of this double-blinded, prospective study will allow a better understanding of the effects and side effects of PSA compared to VIM-DBS in patients with ET.

**Trial registration:**

German Clinical Trials Register: DRKS00004235. Registered on 4 July 2012.

## Background

Essential tremor (ET) is the most common movement disorder with a prevalence of approximately 5 % in a population of 65 years of age and older [1]. ET clinically presents as a bilateral, largely symmetrical postural or kinetic tremor involving hands and forearms [2] and sometimes even the legs, the trunk, or the head and voice. Depending on the severity of the symptoms, ET can lead to significant impairment of activities of daily living [3] and may reduce quality of life [4].

Medical treatment of ET is often unsatisfactory or limited by side effects in up to 50 % of patients with ET [5]. Deep brain stimulation (DBS) is an effective and safe treatment option for pharmacologically resistant ET [6]. The target of choice hitherto has been the ventral intermediate nucleus (VIM) of the thalamus (VIM-DBS) [7]. However, habituation of tremor suppression [8] and stimulation-induced long-term side effects such as gait ataxia [9] or stimulation-induced dysarthria [10] may limit the net benefit of DBS in this target area and reduce individual perception of quality of life.

In recent years, the posterior subthalamic area (PSA), including the prelemniscal radiation and the zona incerta, emerged as a potential new anatomical target to treat ET [11–14] (for a review see Xie et al. [15]). Some studies found a superior effect of PSA stimulation in comparison to VIM stimulation when the same stimulation parameters were used [16–18]. Few studies compared the effect of the two target areas under the best clinical settings: whereas Sandvik et al. found more than half of the best clinical contacts in the PSA [19], Chang et al. compared VIM, PSA, and simultaneous VIM and PSA stimulation and observed no differences in the overall outcome of tremor suppression [20]. Another retrospective, non-randomized study reported 70 % hand tremor reduction in the VIM group and 89 % in the PSA group [21]. Few studies investigated the side effects of PSA stimulation, which can mainly be stimulation-induced dysarthria, gait ataxia, or limb paresthesia contralateral to the stimulation side [22, 23].

So far, to our knowledge, no controlled prospective studies on PSA stimulation in patients with ET with comparison to VIM stimulation are available. To this end, we designed a prospective, controlled pilot study investigating the outcome of PSA stimulation in ET patients. Bilateral electrodes are implanted such that VIM and PSA can be stimulated with different contacts of the same lead to allow a direct comparison of the two target areas in a randomized, double-blinded crossover design. This approach allows comparison of tremor reduction, quality of life, and side effects during PSA stimulation with baseline, as well as with VIM stimulation.

### Study questions

#### Study question 1

Study question 1 asks: Does PSA stimulation reduce tremor severity under PSA-DBS compared to baseline as measured by the Tremor Rating Scale (TRS) [24]? Furthermore, we expect an increase of general and disease-specific quality of life postoperatively (SF-36 [25] and Quality of life in Essential Tremor Questionnaire, QUEST [4]) and a certain degree of stimulation-induced side effects under PSA stimulation such as dysarthria [10] or gait ataxia [9].

#### Study question 2

Study question 2 asks: Does PSA stimulation reduce tremor severity compared to VIM stimulation measured by the TRS in a double-blinded crossover? Although the reports comparing PSA- and VIM-DBS are partially conflicting, we hypothesize a superiority of PSA over VIM stimulation with regard to tremor suppression. As described earlier, this superiority could be eroded due to side effects that might occur under PSA stimulation (so that ideal stimulation parameters cannot be set due to side effects) or due to application of more current in the VIM, thus equalizing the effect on tremor [17]. Due to the overall lack of studies comparing quality of life and DBS-induced side effects between VIM- and/or PSA-DBS, the study remains exploratory, since we were unable to create specific hypotheses for the occurrence of side effects in both regions.

## Methods

### Study design

The study design is illustrated in Fig. 1. After baseline evaluation, patients are implanted as described below (see study procedure). Three months post-implantation, patients enter a double-blinded crossover phase with VIM- and PSA-DBS in randomized order. After 7 months follow-up (7MFU), programming parameters are not restricted until termination of the study at 12MFU.

**Fig. 1 Fig1:**
[figure not shown]
After enrollment and baseline evaluation, patients will be bilaterally implanted with DBS electrodes in the VIM and PSA. The electrodes are placed such that one contact is located on the intercommissural line (*ICL*), the neighboring ventral contact in the PSA, and the neighboring dorsal contact in the VIM. After implantation, the neutral contact on the ICL is activated until 3 months follow-up (*3MFU*). At 3MFU patients are randomized into a blinded crossover phase for 4 months (*gray box*). Depending on randomization, patients receive stimulation in the sequence PSA-VIM or VIM-PSA. Each phase of the crossover starts with a programming visit (*PV*) and ends with an evaluation visit (*EV*). After the blinded crossover phase, the stimulation contacts can be freely chosen until 12MFU

### Study procedure

Patients are screened for study participation and implanted with DBS systems capable of current-controlled (mA) stimulation (Activa RC/PC, Medtronic or Vercise System, Boston Scientific) in the VIM and PSA bilaterally within 6 weeks of study enrollment. Both leads are implanted so that each lead has at least one contact inside the PSA, one inside the VIM, and one ”neutral contact” located on the intercommissural line (ICL, line connecting the anterior with the posterior commissure) in between the two target areas. Between implantation and randomization at 3MFU, this neutral contact is activated and adjusted for optimal tremor suppression with minimal side effects. This is done to ensure that all patients receive the same type of stimulation before entering the randomization phase of the study.

Only if implantation criteria are fulfilled, i.e., both leads are placed as described above and proper lead location is confirmed via stereotactic X-ray or postoperative CT scan, are patients included at 3MFU into the double-blinded, randomized phase of the study. Patients are randomized into two groups (group 1: VIM-DBS followed by PSA-DBS; group 2: PSA-DBS followed by VIM-DBS). The crossover is double-blinded (neither the patient nor the treating neurologist knows which area is stimulated in which period) and lasts for 4 months (2 months on each treatment). A programming visit (PV) is performed at the beginning of each period (at 3MFU and 5MFU) and the best clinical stimulation parameters of the respective contact are determined (i.e., best tremor suppression with no or tolerable side effects). The stepwise increase of current of the electrode contacts in the crossover phase yields a better understanding of the therapeutic windows (i.e., range between effect and side effect) of the two target areas. Double-blinding is also maintained during the programming visit, as adjustment of stimulation parameters is performed by an independent investigator (programmer) as instructed by the blinded rater. An evaluation visit (EV) is performed after each group (EV1 at 5MFU and EV2 at 7 MFU). As the effects and side effects are known to be immediate (although not systematically investigated for VIM-DBS), a longer washout phase between the two crossover phases is not necessary. After the crossover phase, the contact with the best effect and fewest side effects or more complex stimulation paradigms (such as double monopolar or bipolar configurations) can be freely chosen for further treatment until 12MFU.

For study question 1, the change from preoperative to postoperative TRS during 2 months of PSA stimulation will be analyzed. Therefore, the data will be pooled from the EV at 5MFU and 7MFU depending on randomization.

Patients without electrode placement according to the implantation criteria (see above) but with electrodes bilaterally located in the PSA will be stimulated in the PSA directly after implantation, evaluated at 3MFU and 12MFU, and will be excluded from the comparison between PSA and VIM. For the longitudinal PSA effect, 3MFU data from these patients will be pooled with 5MFU and 7MFU data from the randomization group, respectively.

During the entire study the patients are treated with current-controlled (mA) stimulation settings which allow a better comparability of the amount of current applied to the tissue in the crossover design. TRS will be video-recorded for blinded, external analysis of the primary endpoint. Patients not eligible for the study or patients who do not give informed consent for study participation will be treated according to our clinical standard.

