### Outcome measures

The primary endpoint of this study is the reduction of tremor, measured via a reduction in TRS scores, due to PSA-DBS over 2 months compared to preoperative baseline. The TRS is a widely used and well-accepted scale for the clinical assessment of tremor and has been used in most controlled ET studies. The scale was first published in 1993 [24] and validated for ET in 2007 [27]. It consists of three parts: (A) tremor assessment, (B) task assessment, e.g., pouring water from one glass into another, writing, drawing spirals, and (C) a questionnaire assessing activities of daily living, e.g., eating soup with a spoon, social distress, hygiene; the different parts reflect the impairment due to tremor in different dimensions. The TRS has also been used as the primary endpoint measure in the retrospective analysis of Blomstedt et al. [13], which is the basis of power calculation for our study.

Secondary endpoints comprise general (SF-36 [25]) and disease-specific quality of life (QUEST [4], non-validated German version), depression (Beck Depression Inventory, BDI-II [28]), ataxia (International Cooperative Ataxia Rating Scale, ICARS [29]), and the patients’ and physicians’ subjective impressions on tremor severity and side effects (gait and speech) measured via visual analog scale (VAS). Stimulation-induced side effects are determined and recorded as adverse events throughout the study.

In addition, the amount of electric current applied during adjusted stimulation comprises a further endpoint. In case no difference in efficacy is seen between PSA and VIM stimulation in the crossover phase, it is particularly important to detect whether PSA stimulation requires less current on average and if the side effect profile differs in contrast to VIM stimulation. An acoustic speech sample is collected at each visit. The samples are analyzed by a phonetician and speech therapist as previously described [10, 30].

Together, these instruments provide a comprehensive assessment of subjective and objective treatment effects beyond mere motor effect.

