### Handling of missing data

If only one component of a multiple component score (such as TRS part A, B, or C; QUEST part A to E; or SF-36 item groups 3 to 11) is incomplete, the missing item value(s) will be imputed using the most frequent (mode) response to this item in the entire group at the corresponding time point.

If a value measured after DBS is completely missing, the patient will be excluded from the main analysis of the corresponding endpoint. However, in order to guard against bias, a sensitivity analysis is performed reincluding these patients and using multiple imputation methods.

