### Blinding

During the crossover phase the study is performed in a double-blinded design. To ensure that neither the patient nor the physician is aware of the stimulation site (PSA or VIM), during the blinded crossover phase, each patient is seen by a blinded and an unblinded investigator (the latter usually being a study nurse). The unblinded study nurse performs all DBS programming during that phase. The physician decides according to clinical impression whether the stimulation parameters need to be modified (e.g., increase or decrease of amplitude or modulation of pulse width or frequency). The stimulation parameters and especially the activated contact (VIM or PSA) are documented in a separate file not accessible by the blinded physician. The blinded physician will be unblinded after all case report form (CRF) documentation of the crossover phase has been completed.

For the preoperative versus postoperative comparison of tremor suppression, all patients are videotaped and analyzed by an independent rater. The patients wear surgical caps before and after implantation, so that the rater cannot deduce the time point of data collection (i.e., preoperative versus postoperative) from, e.g., scars or short hair after implantation.

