The main strength of this study is the randomization of the patients in the double-blinded crossover phase. Potential limitations of the study are the relatively small sample size and a possible period effect of the crossover. The results of this pilot study need to be confirmed in a larger trial. Like other trials investigating the effects of DBS for the treatment of ET, there are some other DBS-specific methodological limitations. It is commonly accepted that, due to the direct and strong effect of VIM-DBS in ET patients, a truly blinded analysis of the preoperative to the postoperative state is probably impossible [2]. To circumvent this bias, we have designed a double-blinded analysis for the crossover trial comparing VIM and PSA, videotaping the preoperative and postoperative tremor scores for blinded analysis by an independent rater. Assuming that VIM and PSA stimulations do not differ strongly and predictably in effectiveness or side effects, the randomized crossover comparison is thus effectively blinded.

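### The blinded video rating claimed for the primary before/after comparison cannot cover TRS part C, a patient questionnaire, and the protocol does not limit the primary score to the parts a video rater can score

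*Protocol article*

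**What the plan says.** Outcome measures defines the primary endpoint as tremor reduction "measured via a reduction in TRS scores, due to PSA-DBS over 2 months compared to preoperative baseline". The same paragraph describes the TRS as three parts: A is an assessment of tremor, B an assessment of tasks, and the third is "C) a questionnaire assessing activities of daily living, e.g., eating soup with a spoon, social distress, hygiene". Handling of missing data counts all three among the components of a "multiple component score (such as TRS part A, B, or C; QUEST part A to E; or SF-36 item groups 3 to 11". Statistical analysis then works with the TRS score, without naming parts.

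On blinding, Study procedure states that "TRS will be video-recorded for blinded, external analysis of the primary endpoint". The Blinding section says: "For the preoperative versus postoperative comparison of tremor suppression, all patients are videotaped and analyzed by an independent rater". Patients wear caps before and after surgery "so that the rater cannot deduce the time point of data collection". Blinding of the patients themselves is described only for the comparison of targets: "During the crossover phase the study is performed in a double-blinded design".

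The Discussion concedes that fully blind assessment of the state before against the state after surgery is probably out of reach, because the stimulation effect is so strong. It continues: "To circumvent this bias, we have designed a double-blinded analysis for the crossover trial comparing VIM and PSA, videotaping the preoperative and postoperative tremor scores".

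**The concern.** Parts A and B can be scored from a recording by someone who does not know the time point. Part C cannot. Its content is what the patient says about eating, hygiene and social distress, and the patient knows whether surgery has taken place. Filming the interview would not help, since the rater would only be transcribing an unblinded report.

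Study question 1 is an uncontrolled before/after comparison, and independent video rating is its main stated safeguard against expectation. If part C is in the primary score, that safeguard covers only part of the estimate. The size of the effect, and its description as blind-rated, are what is at stake. The trial is also meant to serve as a pilot for a larger multicentre trial, so the estimate may be used again.

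**Working it through.** **1. The statements side by side**

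| Question | Protocol article | Section |
|---|---|---|
| What is the primary endpoint? | Reduction in TRS from preoperative baseline, no restriction by part | Outcome measures |
| What does the TRS contain? | A, B and a questionnaire, C | Outcome measures |
| Is C a component of the score? | Yes, listed with A and B | Handling of missing data |
| How is the primary endpoint blinded? | External analysis of video | Study procedure |
| Who is blinded before/after? | The independent rater, helped by caps | Blinding |
| When are patients blinded? | In the crossover, to target only | Blinding |

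Two readings are possible. If the primary score includes C, the blinding statement is not true of the whole endpoint. If the video rater's score is A+B only, the blinding statement describes a narrower score than the one in Outcome measures. The two sections need reconciling either way.

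**2. Can the bias be sized?**

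Change in total = change in (A+B) + change in C, and change in C = true change in daily function + reporting bias. The article gives only a TRS change from the earlier series, 46.2 − 18.7 = 27.5 points. It gives neither the split between A+B and C nor anything that separates true functional gain from reporting bias. The bias therefore cannot be derived.

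**3. Is the test at risk?**

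Inputs from Sample size and power calculation: SDs 10.1 and 8.8, correlation 0.5, significance level 5 %, power 80 %. Sidedness is not stated; two-sided is assumed here.

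SD of the difference = √(10.1² + 8.8² − 2 × 0.5 × 10.1 × 8.8) = √(102.01 + 77.44 − 88.88) = √90.57 = 9.52.

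Paired t test, noncentral t distribution, difference 27.5: power is 0.720 at n = 3 and 0.957 at n = 4. The plan's n = 4 for question 1 is reproduced.

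Now suppose, purely as an assumption, that part C carried a share of the 27.5 points and is taken out, with the SD held at 9.52:

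| Assumed share of C | Remaining reduction | n for 80 % power | Power at n = 12 |
|---|---|---|---|
| 10 % | 24.75 | 4 | > 0.999 |
| 20 % | 22.0 | 4 | > 0.999 |
| 30 % | 19.25 | 5 | > 0.999 |
| 40 % | 16.5 | 5 | > 0.999 |
| 50 % | 13.75 | 6 | 0.995 |

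The comparison with no reduction keeps ample power throughout. The shares are illustrative and say nothing about what C actually contributes.

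**The case against.** The strongest reply is that the article never writes that the primary endpoint is the total TRS. The Blinding section speaks of tremor suppression and the Discussion of tremor scores, and the missing-data section gives an imputation rule, not an endpoint definition. Which parts the video rater scores could well be settled in the full protocol. This part of the reply stands: a reader might infer that the blinding claim is simply false, but the document supports only the conditional statement that it fails for part C if C is in the score. The point does not vanish, however. The article itself promises blinded analysis of the primary endpoint and defines that endpoint by a scale containing a questionnaire, so this is more than an omitted detail.

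A second reply is that the Discussion already admits the limits of before/after blinding. It does, and this softens the point. The reason given is that a strong effect may betray the time point to the rater. Part C is not mentioned, and video rating is offered as the way round the bias, which it cannot be for a questionnaire.

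Third, patients whose tremor improves should truly report better daily function, so a change in C is not in itself bias. This is correct.

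Fourth, changing the primary endpoint of a trial registered in 2012, with recruitment not completed at submission, is a substantive step. That also stands, and the fix allows for it.

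**Conclusion.** The point holds in conditional form. Unless the primary score for study question 1 is confined to the video-rated parts, which the article does not say, the stated blinding does not extend to the whole primary endpoint. This rests on part C being answered by patients who know their surgical status and on the absence of any restriction to A+B.

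Three stronger inferences are not supported:

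- A reader might turn an assumed share of C into a number of biased points. No split is given, and C's share of the change would not be its bias.
- A reader might set such a figure against the 9-point difference sought in study question 2. Patients there are blinded to target and both evaluations follow surgery, so that comparison is little affected.
- A reader might doubt the significance test for question 1. With half of the planned reduction removed and the SD unchanged, power at n = 12 is still 0.995.

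What is affected is the size and the labelling of the primary estimate. It should be corrected, and wording and reporting are enough to do so.

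**What to change.** - State which TRS parts the independent video rater scores, and who records the rest.
- For study question 1, report the change in video-rated A+B as the blinded result. It can be the primary endpoint or, if the endpoint is to stay as it is, a pre-specified key analysis beside the total.
- Report part C separately as unblinded patient report.
- Describe any total TRS that includes part C as only partly blinded.

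The videos and the rater are already planned, so no new data are needed and power is not threatened. There are two small costs. An A+B score does not match the planning figures from the earlier series exactly, which is a reason to keep the total for comparison. Blind rating of A+B also does not remove expectation effects on the patient's own performance of the tasks, so it should not be presented as full before/after blinding. Making A+B primary would be a formal endpoint change and should be documented as such; the key-analysis option avoids this.
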